### Monitoring, safety and ethical considerations

The study was planned and is conducted in accordance with the International Council for Harmonisation Guideline for Good Clinical Practice [67]. It has been approved by the Institutional Review Board of the Catholic University Eichstätt-Ingolstadt and their local counterparts at all study centers. Data integrity will be monitored by the CTCC. Study safety will be ensured by monitoring for the incidence of serious adverse events (e.g., suicide attempts, unplanned hospitalizations, occurrence of life-threatening conditions) throughout the treatment phase and at post assessment and follow-up. All such incidents and other aspects of study safety will be regularly reported to an independent Data and Safety Monitoring Board, which provides advice on protocol changes in the event of such incidences, or even on discontinuation of the trial. However, no harm to participants is to be expected. In our pilot trial, there was no clinical significant deterioration during treatment [12]. Face-to-face CBT approaches for PGD have been tested in several trials. The control condition, PCT, has not yet been tested in patients with PGD, but in several studies with patients suffering from PTSD, most of them military (active or veterans) or women who had either experienced childhood sexual abuse or multiple victimization in adulthood. In these trials, PCT was received well, with moderate to high pre- to post-treatment effect sizes. Taken together, both treatments, PG-CBT and PCT, seem well suited and beneficial for the trial participants. Still, psychotherapeutic treatment can be emotionally challenging or distressing and might lead to a temporary worsening of symptoms. In the event of clinical deterioration; for example, if a participant were to develop severe suicidal ideation, adequate treatment would be organized. Although the participant would be excluded from the trial in the event of inpatient treatment longer than 2 weeks, they would be free to continue the treatment anytime, if clinically appropriate. Experienced supervisors are available at all trial sites to decide about necessary measures (e.g., referral to inpatient treatment).

All participants are informed about the study in oral and written form, addressing the trials’ procedures, risks, costs, confidentiality, data storage, and the right to discontinue participation at any time and without giving any reasons. Participants are free to continue treatment with their therapists on quitting the research program. For the sake of data completeness, participants who drop out are asked to continue to participate in assessments if they are willing to give reasons for therapy dropout, but can, of course, decline without any further consequences. Treatment costs are covered by health insurance. Participants receive compensation for travel costs arising from diagnostic, but not therapy sessions. In addition, they will receive a small compensation for taking part in post and follow-up assessment (EUR 20 each).

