### Statistical analysis

The primary endpoint will be analyzed using a linear mixed-effect model with baseline adjustment, center as random effect, main effects for group and time, a group-by-time interaction term, and a generalized covariance matrix to account for serial dependency among observations [65]. Stratification randomization factors (study center, type of kinship) will be considered. A parameter of interest is the difference in treatment effect estimated as the difference in mean change *μ* between baseline and follow-up assessments after 12 months between the groups (*H*_0_: *μ*_1_ = *μ*_2_; *H*_1_: *μ*_1_ ≠ *μ*_2_). Confidence intervals (95%) for the point estimate for the difference in mean change will be given as well as the standard error. The primary analysis will be done according to the intention-to-treat principle. Missing values, a potential source of bias, will be considered in line with the framework of Rubin [66]. The effects of potentially necessary modeling strategies (i.e., regression computational methods, multiple imputation) for missing values of the primary outcome will be contrasted through sensitivity analyses. A further sensitivity analysis will be based on the per-protocol population (defined as all randomized patients without any major protocol violations). Further analyses will include covariates of prognostic importance in the linear mixed-effect model. For the secondary endpoints, the statistical analysis will be performed as described above. Whenever possible multivariate testing is preferred, especially with closely related predictors (e.g., rumination and negative cognitions). The most promising predictors according to regression analyses will be further evaluated in mediator analysis.

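### Excluding participants from the trial after more than 2 weeks of inpatient treatment does not fit the intention-to-treat primary analysis, and the text does not secure their 12-month outcome

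*Protocol article*

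**What the plan says.** All places are in the Methods of the protocol article.

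- **Monitoring, safety and ethical considerations.** The rule follows a sentence on deterioration: "In the event of clinical deterioration; for example, if a participant were to develop severe suicidal ideation, adequate treatment would be organized". It then reads "Although the participant would be excluded from the trial in the event of inpatient treatment longer than 2 weeks", and the sentence ends "they would be free to continue the treatment anytime, if clinically appropriate".
- **Same section, on safety.** Study safety rests on "monitoring for the incidence of serious adverse events (e.g., suicide attempts, unplanned hospitalizations, occurrence of life-threatening conditions"). This runs through the treatment phase and on to the post and follow-up assessments, with reports to an independent monitoring board.
- **Same section, on dropouts.** To keep the data complete, "participants who drop out are asked to continue to participate in assessments if they are willing to give reasons for therapy dropout". The Procedure section similarly offers the post-treatment self-report measures to willing dropouts.
- **Statistical analysis.** "The primary analysis will be done according to the intention-to-treat principle". On missing data: "Missing values, a potential source of bias, will be considered in line with the framework of Rubin", with strategies such as multiple imputation compared in sensitivity analyses. The per-protocol set is a further sensitivity analysis, "defined as all randomized patients without any major protocol violations".
- **Primary outcome.** PG-13 severity from a blinded interview 12 months after randomization.

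**The concern.** Intention to treat requires that every randomized participant counts in the allocated arm, with the primary outcome sought whatever happens in between. The inpatient rule removes people because of something that happens after randomization. Its setting in the text is clinical deterioration, so those removed probably fare differently from those who stay.

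Two things are at stake. First, if the 12-month PG-13 is not obtained for these participants, the loss is related to outcome and may differ between an exposure-based and a supportive therapy. A missing-at-random assumption is least credible for exactly these people. Second, safety events that occur after exclusion may go unrecorded in participants who have already had a long inpatient stay.

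**Working it through.** **1. Does the exclusion concern treatment or the trial?** The rule and the permission to continue treatment stand in one sentence. If only therapy were meant, the second half would contradict the first. The dropout paragraph draws the same line, since participants may stay with their therapist after leaving the research. The natural reading is that trial participation ends.

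**2. Does another provision keep these participants in follow-up?**

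| Provision | Whom it addresses | Covers participants excluded by the trial? |
|---|---|---|
| Procedure: post-treatment measures | Dropouts who are willing | Not expressly |
| Monitoring section: continued assessments | Dropouts from therapy, if willing | Not expressly |
| Statistical analysis: intention to treat | The primary analysis | Implied by the principle, but at odds with the exclusion |
| Statistical analysis: per-protocol set | Participants without major violations | A possible place for the event, but the rule does not refer to it |

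No statement says that these participants have the 12-month interview or stay in the primary analysis. None says the opposite either.

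**3. The plan's own sample size, which supplies the scale.** Inputs from Sample size: difference 5.5 points, SD 13, r = 0.3, power 0.80, alpha 0.05. Two-sided testing follows from the hypotheses in Statistical analysis. A 1:1 allocation is assumed.

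- Adjusted SD = 13 × √(1 − 0.3²) = 12.40.
- Normal approximation: n per arm = 2 × (1.96 + 0.84)² × 12.4² / 5.5², rounded up to 80, total 160. The t-test version gives 161.5, hence 162, as stated.
- Dropout: 162 / 0.80 = 202.5, so 203, or 204 with equal arms, as stated.

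These figures reproduce, and the point does not change them.

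**4. Possible shift if only those remaining are analysed.** Let f1 and f2 be the excluded shares in PG-CBT and PCT, and let D be the number of points by which the excluded improve less than the others. The true mean improvement in an arm is (1 − f)·m + f·(m − D) = m − f·D, where m is the mean among those who remain. Using m overstates the arm by f·D, so the group difference shifts by D × (f1 − f2).

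The article gives neither f nor D. Assumed: D = 5.5 (the target difference) or 13 (one unadjusted SD).

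| f1 | f2 | D | Shift (points) | Share of 5.5 |
|---|---|---|---|---|
| 5% | 2% | 5.5 | 0.03 × 5.5 = 0.165 | 3% |
| 5% | 2% | 13 | 0.03 × 13 = 0.39 | 7% |
| 5% | 0% | 5.5 | 0.05 × 5.5 = 0.275 | 5% |
| 5% | 0% | 13 | 0.05 × 13 = 0.65 | 12% |
| 5% | 5% | 5.5 or 13 | 0 | 0% |

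With f1 = 2% and f2 = 5% the first two shifts change sign. The arm with more exclusions is the one favoured.

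**5. Power.** If 5% are lost on top of the planned 20%, 204 × 0.80 × 0.95 / 2 = 77.5 per arm remain, and power is 0.789 (normal approximation) against the planned 0.80. The loss of precision is minor.

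**The case against.** The best case for the plan is that the rule is one clause in a safety paragraph of a condensed article. The Statistical analysis section sets intention to treat as primary and leaves protocol violations to a sensitivity analysis. Dropouts are asked to stay in assessments, and missing data are recognised as a source of bias. On this view the wording is loose, and the full protocol may settle it.

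Part of this stands. A reader might infer that the 12-month PG-13 is not collected, that data are discarded, or that these participants leave the analysis set. The article says none of this. A reader might also infer that the rule removes the worst outcomes. That comes from the deterioration context, whereas the clause turns on length of inpatient stay, not on PG-13 severity. Nor is a biased comparison of harms shown. An unplanned hospitalization that triggers the rule is itself a listed serious adverse event and would be reported, so only later events are at risk.

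A much larger bias is not supported either. Acute suicidality, psychotic disorder and severe substance use disorder are exclusion criteria, and the pilot saw no clinically significant deterioration during treatment. The Procedure section also has PG-13 taken after sessions 5, 10 and 15. If those values enter the mixed model, worsening before exclusion is partly reflected, and the completers-only formula overstates the shift.

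What does not stand is the defence by omission. The point rests on a rule the article states, not on a detail it leaves out. The dropout provisions concern people who leave therapy, while this rule lets therapy continue and ends trial participation.

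**Conclusion.** The point holds as a conflict between stated rules. Read as written, the inpatient rule is a post-randomization, probably outcome-related exclusion that does not fit the intention-to-treat primary analysis, and no provision expressly keeps these participants in follow-up. Their 12-month PG-13 and later safety events may be lost. Whether they would be is not stated.

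The numerical effect is probably small. It is about 0.2 to 0.65 points, or 3 to 12% of the 5.5-point target, if excluded shares differ by 3 to 5 percentage points, outcome gaps are 5.5 to 13 points, and only completers are analysed. All of these are assumptions. The case for a change rests on the conflict and on how easily the loss can be avoided, not on the upper end of this range. Imputation cannot fully replace an interview that could have been held.

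**What to change.** Reconcile the inpatient rule and the dropout paragraph (Monitoring, safety and ethical considerations) with the Statistical analysis section. Replace the clause that excludes the participant from the trial by a statement to this effect:

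- A participant with such an inpatient stay remains in the trial for data purposes, subject to continued consent.
- The post-treatment assessment, the blinded 12-month PG-13 and the serious-adverse-event assessments are attempted on the original schedule.
- The participant is analysed in the allocated arm. The event counts at most towards the definition of the per-protocol set.

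The clinical rule on treatment stays as it is, and no view is taken on the 2-week limit. The cost is a short amendment and a few extra follow-up interviews by existing raters. The sample size does not change.

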### Sample size

Given the large effect size found in our pilot study (Cohen’s *d* = 1.32) for comparing PG-CBT to a waiting-list condition [12], and the smaller yet substantial effect sizes found in studies comparing a grief-specific treatment with less specific (0.37; [34]) or supportive control groups (0.40; [13]), the assumption of an effect size of at least *d* = 0.42 seems reasonable when comparing the integrative, grief-specific PG-CBT to the unspecific PCT control condition. Therefore, power calculation for the primary endpoint of this trial is based on the assumption that PG-CBT is more effective, if a minimal clinical relevant difference of 5.5 points (PG-13 symptom severity) in mean change between baseline and 12-month follow-up could be shown between the groups. We expect the variance of the PG-CBT group to exceed that of the pilot study. The assumed *SD* = 13 is reduced by the factor [(1 – *r*^2^)]^1/2^ to a baseline-covariate adjusted *SD* = 12.4 with correlation of *r* = 0.3 in this multicenter study with a 12-month follow-up (pilot trial after approximately 6-month follow-up: *r* = 0.4). A total sample size of *N* = 162 is needed to detect the minimal clinical relevant difference between the two groups with a power of 0.80 and an alpha of 0.05. We aim to recruit 204 patients to allow for an estimated dropout rate of 20%.

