### Procedure

Interested participants, who are potentially eligible (i.e., death of a significant other at least 6 months previously and aged 18 to 75 years), are invited to a first clinical interview. If an individual does not present severe mental symptoms that warrant immediate clinical attention (e.g., acute suicidal ideation assessed using the Columbia-Suicide Severity Rating Scale; CSSRS; [35]) and scores 20 points or more on a screener for PGD symptoms, the ICG-D (Inventory of Complicated Grief; see below), they receive oral and written information about the trial and are invited for baseline assessment. In baseline assessment (after individuals have given their written informed consent), a trained rater assesses PGD diagnosis (PG-13) and comorbidity using the German version of the Structured Clinical Interview for DSM-IV Axis-I Disorders (SCID-I; [36]). In addition, cognitive functioning is tested with the Mini Mental State Examination (MMSE-2; [37]) with individuals aged over 50 years. Self-report measures are given to the participants to be completed at home. If an individual is eligible, randomization is requested of the CTCC before a third appointment. The potential participant is then informed about the randomization result. Thus, the allocation sequence is concealed from the investigators until actual randomization. If an individual does not fulfill the eligibility criteria, or withdraws their consent after randomization, they are counseled about treatment alternatives. Trained raters blinded for treatment allocation conduct the baseline and all further assessments. During treatment, participants complete the PGD screener before each session, while therapists complete a short session screener afterwards, concerning session content including a list of possible serious adverse events. In addition, after sessions 5, 10 and 15, PGD is assessed with the PG-13 and instruments measuring secondary and tertiary outcomes/possible mediators are administered. At post treatment (or in case of dropout if the participant is willing), self-report measures are given to the participant to fill in at home. PGD diagnosis is assessed in a diagnostic interview scheduled after the last treatment session. Follow-up diagnostic takes place 12 months after randomization. See Fig. 2 for an overview of measures and assessment points.

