### Interventions

Both interventions are manualized treatments that encompass 20 individual sessions, with the option of four additional sessions to cover special occasions or needs (e.g., another loss or an anniversary). Consequently, the overall treatment dose is flexible from 20 to 24 sessions. In addition, if the patient and therapist feel that the treatment goals have been reached, therapy might be finished earlier. Nonetheless, therapists are asked to stick to the respective treatment manuals concerning content and sequence of sessions. Sessions are scheduled weekly whenever possible, a session lasting 50 min, although some sessions can be combined (100 min). The overall length of treatment is about 6 months.

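### Read literally, therapy dropouts are asked for the 12-month PG-13 only on condition that they explain why they left, an avoidable filter on the primary outcome

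*Protocol article*

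**What the plan says.** Three places in the protocol article bear on follow-up after therapy dropout.

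- **Monitoring, safety and ethical considerations.** Participants are told of "the right to discontinue participation at any time and without giving any reasons". A little further on, the retention rule opens with its purpose, "For the sake of data completeness, participants who drop out are asked to continue to participate in assessments", and then attaches a condition. In full, "participants who drop out are asked to continue to participate in assessments if they are willing to give reasons for therapy dropout"; they may decline without consequences.
- **Procedure.** For the questionnaires the rule is "At post treatment (or in case of dropout if the participant is willing), self-report measures are given to the participant to fill in at home". For the interview, "PGD diagnosis is assessed in a diagnostic interview scheduled after the last treatment session". The follow-up assessment is tied to randomization, at 12 months, and not to the end of therapy.
- **Sample size.** Recruitment is raised from 162 to 204 "to allow for an estimated dropout rate of 20" per cent. The article does not say whether this means stopping therapy or having no 12-month assessment.

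Under Primary outcome, the endpoint is PG-13 severity at the 12-month follow-up. Under Statistical analysis, the primary analysis follows intention to treat, missing values are acknowledged as a possible source of bias, and sensitivity analyses including multiple imputation are planned.

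**The concern.** The primary endpoint is timed from randomization, so a patient who stops therapy in week 5 can still supply it. Whether that happens depends on whether the patient is asked. As worded, those unwilling to explain themselves are not asked, and unwillingness to explain is unlikely to be a random trait. Someone who found the treatment distressing, or who felt no better, may be both less willing to say so and worse at 12 months.

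The arms also differ in ways that could affect this. PG-CBT has nine central sessions on exposure and cognitive restructuring, PCT has no exposure, and the article accepts that therapy can be distressing and bring temporary worsening. Loss through the filter could therefore differ by arm as well as by outcome. Under standard assumptions, the multiple imputation named in the plan corrects for loss that observed data explain. A reason that the patient declined to give is not among those data.

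At stake is the completeness on which the intention-to-treat comparison of the primary outcome relies.

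**Working it through.** **1. The plan's own sample size.** Inputs from Sample size: difference 5.5, SD 13, r = 0.3, power 0.80, alpha 0.05. The test is taken as two-sided, from the hypotheses under Statistical analysis; 1:1 allocation is assumed.

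- Adjusted SD = 13 × √(1 − 0.3²) = 12.40.
- Two-sample t-test: 80.76, so 81 per arm, total 162. This matches.
- Dropout: 162 / 0.8 = 202.5, so 203, or 204 as an even total. This matches the target.

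**2. Power by share with 12-month data** (102 per arm randomized, difference 5.5, SD 12.4, t-test):

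| Share with 12-month PG-13 | Power |
|---|---|
| 100% | 0.88 |
| 90% | 0.85 |
| 80% | 0.80 |
| 70% | 0.75 |

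The allowance holds if at least about 80% are assessed at 12 months, whatever share stops therapy.

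**3. Bias from selective loss.** Let a share m of an arm be unobserved, with a mean D points worse than the observed patients in that arm. The arm's true mean is

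(1 − m) × observed + m × (observed + D) = observed + m × D,

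so the observed mean is too favourable by m × D. With a common D, the between-arm difference is off by

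bias = D × (m₁ − m₀).

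The documents give neither D nor dropout by arm. The following values are assumptions: D from 3 to 8 points, no dropout followed up, and nothing in the baseline or interim scores explaining the gap.

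| Dropout by arm | D = 3 | D = 8 | Share of 5.5 |
|---|---|---|---|
| 20% / 20% | 0 | 0 | 0 |
| 25% / 15% | 3 × 0.10 = 0.3 | 8 × 0.10 = 0.8 | 5.5% to 14.5% |
| 30% / 10% | 3 × 0.20 = 0.6 | 8 × 0.20 = 1.6 | 10.9% to 29.1% |

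If only half of the dropouts in each arm are lost, each figure halves (0.15 to 0.8 points for the last two rows). More unobserved loss in PG-CBT would flatter PG-CBT; more in PCT would hide part of a real benefit.

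**4. The two dropout passages side by side.** The Procedure passage also mentions dropouts and makes no reference to reasons, only to willingness. But it concerns the self-report measures handed out at post treatment or at dropout. It does not cover the 12-month interview, so it does not remove the condition from the retention rule.

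**The case against.** **The sentence may be loosely written.** It opens with data completeness and ends with the freedom to decline, and the same section guarantees leaving without reasons. The authors may have meant that dropouts are asked to stay in assessment and, if willing, to say why they left. That reading is possible, but it is not what the words say, and sites could apply the restrictive version. If the loose reading was meant, the correction costs nothing.

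**The analysis plan already addresses missing data.** It does: intention to treat, a mixed model, sensitivity analyses, and PG-13 assessments after sessions 5, 10 and 15 that could inform the model if included. This reduces the concern. None of the methods named deals with loss that depends on unobserved outcomes, and a collected outcome is better than a modelled one.

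**Stronger readings that the document does not support.**

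- A reader might infer that missingness *is* selective. It is a risk; no dropout or outcome data by arm are given, and equal loss with equal gaps gives no bias.
- A reader might take 20% loss with a 6.5-point gap (half of SD 13) in one arm and none in the other, giving 0.20 × 6.5 = 1.3 points. That is a single unfavourable case, and no figure in the article supports its one-sided gap.
- A reader might expect the evaluable number to rise from about 163 (204 × 0.8) to about 184 if half of the dropouts were assessed. This presumes that no therapy dropout is assessed now, whereas even the literal sentence keeps those who give reasons. The 20% may also already mean lost assessments.
- A reader might say that dropouts' post-treatment questionnaires are mistimed, much like carried-forward values. They are real measurements. Post treatment is tied to the end of therapy for everyone, and "if the patient and therapist feel that the treatment goals have been reached, therapy might be finished earlier", so completers are not all measured at 6 months either. How such values are coded is commonly left to the SAP. Only secondary outcomes are touched.

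**Conclusion.** The point holds as a defect of wording with a possible effect on the primary outcome. The retention rule, read literally, ties the request for the 12-month PG-13 to giving reasons. This works against the rule's own purpose, sits awkwardly beside the right to leave without reasons, and is a poor match for intention to treat. It should be changed.

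The resulting bias is of unknown size and direction: none if loss and gaps are equal across arms, and about 0.3 to 1.6 points in the unequal-dropout cases worked above. That range rests on assumed gaps, assumed dropout by arm, no follow-up of dropouts and no help from interim scores, so its upper end is not a forecast. The sample-size figures stand.

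The timing of dropouts' questionnaires is a minor matter for the secondary post-treatment outcomes. The primary outcome keeps its fixed date.

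**What to change.** **Main change.** In Monitoring, safety and ethical considerations, delete the condition. State that every randomized patient who stops therapy and has not withdrawn consent to assessment is asked to attend the blinded 12-month PG-13, whether or not reasons are given. Ask for reasons as a separate, optional question. Patients who withdraw consent, including after learning their allocation, can be approached only as far as their consent allows. All keep the right to decline.

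**Minor addition.** In Procedure, require the actual date of any questionnaire completed at dropout to be recorded, so that the analysis of post-treatment secondary outcomes can use its real time.

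**Cost.** Revised wording in two places and a few more interviews by the existing raters. The EUR 20 payment for the follow-up assessment is already provided for. Some patients will still decline, so the planned missing-data analyses remain necessary.
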